## 6.6 Statistical analyses during the course of the study

A conditional sample size estimation is performed why estimated values of allogeneic transfusion rate in the test and control group will be confirmed in an interim analysis when 150 patients have completed the study. If the normal transfusion rate of allogeneic blood is lower than 21% or the

transfusion rate in the test group is higher than 7% the study risk being inconclusive. In such cases additional patients may be considered after approval from the IEC.

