## 6.2 Description of outcome variables in relation to objectives and hypotheses

The primary variable, transfusion rate, will be measured as the proportion ( $\pi$ ) of patients in each treatment group that is receiving allogeneic blood transfusion of the total number of patients in each treatment group. The hypothesis to be tested is:

$$H_0 = \pi_s = \pi_c$$

versus

$$H_1 = \pi_s \neq \pi_c$$

Where:

$\pi_s$  = Proportion patients treated with Sangvia® that require allogeneic blood transfusion in addition to Sangvia® transfusion.

$\pi_c$  = Proportion patients in the control group that require allogeneic blood transfusion.

The hypothesis will be tested using the Fischer Exact Test. The hypothesis will be rejected if the p-value is  $\leq 0.05$ .

Secondary objectives will be tested using similar hypotheses. The total and variable specific proportion values for infection rate, use of post-operative antibiotics and adverse events will be tested between the groups using the Fischer Exact Test. Continuous variables (e.g. post-op Hb values) will be compared and tested using the Wilcoxon Rank Sum test. Laboratory blood markers will also be evaluated for changes over time within each treatment group and this change will be tested using the Wilcoxon Signed Rank test.

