## 6.5 Determination of sample size

The primary variable and objective is the base for the sample size calculation. The sample size formula used is referred to in Lachin 1981.

$$N = \frac{(Z_{\alpha} + Z_{\beta})^2 4\bar{\pi}(1 - \bar{\pi})}{(\pi_s - \pi_c)^2}$$

Where:

N = total number of patients

$Z_{\alpha} = 1.96$  ( $\alpha = 0.05$ )

$Z_{\beta} = 1.2816$  ( $1 - \beta = 0.90$ )

$$\bar{\pi} = \frac{\pi_s + \pi_c}{2}$$

An estimation normal use of allogeneic blood of 21% is based on reported values in the literature. It is acknowledged that in revision surgery a higher percentage of allogeneic blood transfusions is seen than in primary total hip replacements. Because revision patients requiring serious bone grafting are excluded, the percentage of revision patients is expected to be just slightly higher than for the average primary total hip. A high number of revision, e.g. a maximum of 30%, in the total group of patients is considered to have limited effect of the total transfusion rate but are accounted for in the 21% assumed for the total group. The expected values of transfusion rate in the Sangvia® group is estimated to lie around 7%. Accordingly, imputing the values for the estimated transfusion rates in the test and control group generates a mean transfusion rate value of 14%. The sample size necessary for detection of this expected difference in transfusion rate frequency is calculated to 260 patients (5% significance level, two-sided hypothesis, 90% power). Additional 40 patients will be included in the study to compensate for drop-out. In summary, 300 patients will be included in total and 150 in each treatment group.

The transfusion rate of bank blood is considered to vary dependent on type and complexity of surgery. Greatest normal use and differences between the groups are expected in the subgroup with medium (surgery duration 1-2 hours) to complex (surgery duration more than 2 hours) surgery complexity why power are considered to be adequate for the planned subgroup analyses in these groups.

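### The interim rule in section 6.6 signals trouble in about 70% of trials that are exactly on plan, and opens an unbounded sample-size increase after arm-level rates are seen

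*Protocol*

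**What the plan says.** Section 6.5 sets the planning values. For control: "An estimation normal use of allogeneic blood of 21% is based on reported values in the literature". For the test arm: "The expected values of transfusion rate in the Sangvia® group is estimated to lie around 7"%. At "5% significance level, two-sided hypothesis, 90% power" the required "difference in transfusion rate frequency is calculated to 260 patients", and "Additional 40 patients will be included in the study to compensate for drop-out", which gives 300 in total and 150 per arm.

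Section 6.6 then states that the "estimated values of allogeneic transfusion rate in the test and control group will be confirmed in an interim analysis when 150 patients" reach the end of follow-up. If control is below 21%, or the "transfusion rate in the test group is higher than 7% the study risk being inconclusive", and extra patients may be considered once the ethics committee approves. The section gives no tolerance around the two values, no formula for the increase and no maximum. It does not say who sees the rates.

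On the final analysis, section 6.2 says "The hypothesis will be tested using the Fischer Exact Test" and rejects at p ≤ 0.05. Section 6.4 repeats that level. Neither mentions the interim look.

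**The concern.** The rule compares each arm's observed rate with its own planning value and joins the two comparisons with an *or*. If the planning values are correct, each observed rate falls on the wrong side nearly half the time by chance, so a warning is the usual result of a trial that is going to plan.

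The rule also disagrees with the protocol's own sample-size reasoning. In section 6.5 the required number depends on the two rates jointly, through their difference and their mean. A test rate of 10% is no threat if control is 30%, yet section 6.6 flags it.

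Applying the trigger requires both arms' rates, so whoever applies it sees the interim treatment effect. The size of any increase is then left open, and the final test is unadjusted. At stake are whether the decision to enlarge rests on anything but noise, and whether the error rate of the final test can be stated in advance.

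**Working it through.** **Inputs.** 21% and 7%, two-sided 5%, 90% power, 260 evaluable, 40 extra, 300 in total, 1:1 (section 6.5). Look at 150 completed (section 6.6). Fisher exact test at p ≤ 0.05 (sections 6.2 and 6.4). Assumed: the 150 split as 75 and 75.

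**1. The plan's own figure.** N = (1.96 + 1.2816)² × 4 × p̄(1 − p̄) / (difference)². For 21% v 7%: 10.508 × 4 × 0.14 × 0.86 / 0.14² = 258.2. The stated 260 is reproduced.

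**2. How often the trigger fires when the plan is right.** Since 0.21 × 75 = 15.75, control is below 21% at 15 or fewer events. Since 0.07 × 75 = 5.25, the test arm is above 7% at 6 or more.

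- P(X ≤ 15 | 75, 0.21) = 0.483
- P(X ≥ 6 | 75, 0.07) = 0.429
- Either: 1 − (1 − 0.483)(1 − 0.429) = 0.705

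Splits of 70/80 and 80/70 (control/test) give 0.740 and 0.764, so the result does not depend on an exact 75/75 split.

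**3. Whether the trigger tracks the required N.** The same calculation for other true rates, beside the section 6.5 formula:

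| True control / test | N by section 6.5 | P(trigger) |
|---|---|---|
| 21% / 7% | 258 | 0.705 |
| 25% / 7% | 174 | 0.540 |
| 30% / 10% | 168 | 0.781 |
| 30% / 7% | 120 | 0.449 |
| 21% / 10% | 455 | 0.883 |

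A trial that needs 168 patients is flagged more often than one that needs 258. Among triggers at 21%/7%, 29% occur with an observed difference of at least the planned 14 points. In 43%, the section 6.5 formula applied to the observed rates asks for 300 or fewer.

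**4. Type I error of the planned test.** Exact enumeration of interim and final outcomes under a common rate in both arms, Fisher test at p ≤ 0.05:

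- No increase (150 per arm), common rate 14%: 3.4%.
- Every trigger leads to a fixed increase to 200–450 per arm, common rate 14%: 3.6% to 4.0%.
- New N chosen from the observed difference to favour rejection, up to 600 in total: 4.6% at a common rate of 14%, 4.7% at 21%, 4.9% at 30%.
- The same, up to 900 in total: 5.0%, 5.2% and 5.4% at those rates.

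Fisher's test is conservative at these rates, and that margin absorbs most of the inflation. A chi-square-type test would have no such margin: about 6.6% in the last scenario.

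**5. A blinded alternative.** Use the pooled rate p̄ and hold the planned ratio 7/21, so control = 1.5p̄ and test = 0.5p̄. The section 6.5 formula gives evaluable N = 378 at 10%, 308 at 12% and 258 at 14%. Multiplying by 300/260 for drop-out gives about 436, 356 and 298 enrolled; the last stays at 300.

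**6. What the blinded version misses.** With true rates of 21% and 10%, the pooled rate is 15.5% and the rule returns 229, while the formula at the true rates needs 455. The trial would stay at 300, where exact Fisher power is 71% even with all 300 evaluable.

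**The case against.** The strongest defence is that section 6.6 compels nothing. The trigger prompts a discussion, extra patients need ethics committee approval, and no interim hypothesis test or early stop for efficacy is planned. A reader might infer from the 70% figure that 70% of on-plan trials would be enlarged. The text does not support that: 70% is the chance of a warning, not of an increase.

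A reader might also infer that the final p-value is materially invalid. For the test actually planned it is not. Error above 5% needs an N picked to favour rejection, a ceiling near 900 and common rates of about 21% or more.

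Nor do the documents show that interim rates reach those who decide on transfusion. Section 3.6.1 assigns those decisions to an assessor unaware of allocation whenever possible, with blinded review of the rest. Section 6.6 is silent on who sees the rates, and that can reasonably be settled elsewhere.

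Waiting until 150 patients have completed the study, although transfusion need is assessed only to discharge (section 4.2.1.1), costs little when N can only rise. The rule is also sensitive: it stays silent only if the observed difference is at least (16 − 5)/75 = 14.7 points.

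All of this stands, and it limits the harm. It does not rescue the trigger. A warning expected in seven of ten on-plan trials tells an ethics committee almost nothing, and the protocol itself fixes it, so this is not detail left to an analysis plan.

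**Conclusion.** The point holds as a flaw in a stated rule and should be fixed. The trigger fires in about 70% of trials whose assumptions are exactly right, and in 54% to 78% of trials at 25%/7% and 30%/10%, where the required N is 174 and 168. It contradicts the joint dependence on both rates in section 6.5. The increase that it opens has no formula or limit, follows sight of arm-level rates, and leaves the final level untouched.

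The consequence for type I error is small: 3.4% with no increase, at most 4.9% in the cases computed up to 600 patients, and 5.2% to 5.4% only in the contrived cases up to 900.

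The trigger figures rest on roughly equal arms at the look. The type I figures rest on the Fisher test being kept and on the common rates shown.

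**What to change.** Delete the 21%/7% trigger from section 6.6 and prespecify one rule that uses the section 6.5 formula. It should only move upward from 300, apply the drop-out allowance (300/260), and name a maximum N before the look.

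**Simplest version, blinded.** Once 150 patients have been discharged, compute only the pooled transfusion rate, hold the 7/21 ratio and recalculate N. The final test then needs no penalty. The cost is one rewritten paragraph and the loss of arm-specific rates at mid-trial. The paragraph should state the limitation openly: this rule corrects a wrong overall event rate but cannot detect a treatment effect smaller than planned, as the 21%/10% case shows.

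**If the sponsor wants to keep arm-level rates.** Someone independent of the sites should apply the formula to both rates jointly, with a fixed maximum and a final test that controls type I error for the increase. This keeps the ability to react to a smaller effect, at the price of an independent analyst and a more elaborate final analysis.

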## 7 STUDY MANAGEMENT

### 7.1 Monitoring

Before first subject enters into the study, a representative of Astra Tech will visit the investigational study site to:

- Determine the adequacy of the facilities
- Discuss with the investigator(s) (and other personnel involved with the study) their responsibilities with regard to protocol adherence, and the responsibilities of Astra Tech or its representatives. This will be documented in a Clinical Study Agreement between Astra Tech and the investigator

During the study, a monitor from Astra Tech or company representing Astra Tech will have regular contacts with the study site, including visits to:

- Provide information and support to the investigator(s)
- Confirm that facilities remain acceptable
- Confirm that the investigational team is adhering to the protocol, that data are being accurately recorded in the CRFs, and that investigational product accountability checks are being performed
- Perform source data verification (a comparison of the data in the CRFs with the subject's medical records at the hospital or practice, and other records relevant to the study). This will require direct access to all original records for each subject (e.g., clinic charts).

The monitor or another Astra Tech representative will be available between visits if the investigator(s) or other staff at the centre need information and advice.

### 7.2 Audits and inspections

Authorized representatives of Astra Tech, a regulatory authority, an Ethics Committee may visit the centre to perform audits or inspections, including source data verification. The purpose of an Astra Tech audit or inspection is to systematically and independently examine all study-related activities and documents to determine whether these activities were conducted, and data were recorded, analyzed, and accurately reported according to the protocol, ISO 14155, Good Clinical Practice (GCP) and any applicable regulatory requirements. The investigator should contact Astra Tech immediately if contacted by a regulatory agency about an inspection at his or her centre.

## 7.3 Training of staff

The principal investigator will maintain a record of all individuals involved in the study (medical, nursing and other staff). He or she will ensure that appropriate training relevant to the study is given to all of these staff, and that any new information of relevance to the performance of this study is forwarded to the staff involved.

## 7.4 Changes to the protocol

Study procedures will not be changed without the mutual agreement of the principal investigators and Astra Tech. If it is necessary for the study protocol to be amended, the amendment and/or a new version of the study protocol (Amended Protocol) must be notified to or approved by each Ethics Committee, and if applicable, also the local regulatory authority, before implementation. Local requirements must be followed. If a protocol amendment requires a change to a particular centre's Informed Consent Form, then Astra Tech and the centre's Ethics Committee must be notified. Approval of the revised Informed Consent Form by Astra Tech and by the Ethics Committee is required before the revised form is used.

Astra Tech will distribute administrative changes, amendments and new versions of the protocol to each principal investigator.

## 7.5 Study agreements

The principal investigator at each centre must comply with all the terms, conditions, and obligations of the Clinical Study Agreement for this study. In the event of any inconsistency between this Clinical Study Protocol and the Clinical Study Agreement, the Clinical Study Protocol shall prevail. In the event of any inconsistency between translations of the Clinical Study Protocol and/or the Clinical Study Agreement, the original English versions of the Clinical Study Protocol and the Clinical Study Agreement shall prevail.

## 7.6 Study timetable

Before a subject's enrolment in the study and any study-related procedures are undertaken the following should be fulfilled:

- Signed Clinical Study Protocol and other agreements between Astra Tech and the Principal Investigator/Study Site.
- Approval of the study by the Ethics Committee

Date of first subject enrolled is estimated to 28th February 2009 and date of last subject completed is estimated to the 30th November 2009.

## 8 ETHICS

### 8.1 Ethics review

Astra Tech will provide Ethics Committees and Principal Investigators with safety updates/reports according to local requirements.

The final study protocol, including the final version of the Informed Consent Form, must be approved or given a favorable opinion in writing by an Ethics Committee as appropriate. The investigator must submit written approval to Astra Tech before he or she can enroll any subject into the study.

The Principal Investigator is responsible for informing the Ethics Committee of any amendment to the protocol in accordance with local requirements. In addition, the Ethics Committee must approve all advertising used to recruit subjects for the study.

The Principal Investigator is also responsible for providing the Ethics Committee with reports of any SAEs (or ADEs) from any other study conducted with the investigational product. Astra Tech will provide this information to the Principal Investigator.

Progress reports and notifications of SAEs (and ADEs) will be provided to the Ethics Committee according to local regulations and guidelines.

### 8.2 Ethical conduct of the study

The study will be performed in accordance with ethical principles that have their origin in the Declaration of Helsinki and are consistent with ISO 14155 and Good Clinical Practice and applicable regulatory requirements.

### 8.3 Informed consent

The principal investigator(s) at each centre will ensure that the subject is given full and adequate oral and written information about the nature, purpose, possible risk and benefit of the study. Subjects must also be notified that they are free to discontinue from the study at any time. The subject should be given the opportunity to ask questions and allowed time to consider the information provided.

The subject's signed and dated informed consent must be obtained before conducting any procedure specifically for the study, including the following:

The principal investigator(s) must store the original, signed Informed Consent Form in the ISF. A copy of the signed Informed Consent Form must be given to the subject.

If modifications are made according to local requirements, the local version has to be approved by Astra Tech.

## 8.4 Subject data protection

The Master Informed Consent Form will incorporate (or, in some cases, be accompanied by a separate document incorporating) wording that complies with relevant data protection and privacy legislation. Pursuant to this wording, subjects will authorize the collection, use and disclosure of their study data by the Investigator and by those persons who need that information for the purposes of the study.

The Master Informed Consent Form will explain that study data will be stored in a computer database, maintaining confidentiality in accordance with national data legislation. All data computer processed by Astra Tech will be identified by a study code and a Subject ID.

The Master Informed Consent Form will also explain that for data verification purposes, authorized representatives of Astra Tech, a regulatory authority, an Ethics Committee may require direct access to parts of the hospital or practice records relevant to the study, including subjects' medical history.

### 9.2 Pregnancy

Pregnancy itself is not regarded as an AE/ADE unless there is a suspicion that the medical device under study may have interfered with the effectiveness of a contraceptive medication.

Congenital abnormalities/birth defects and spontaneous miscarriages should be reported as SAEs.  
Elective abortions without complications should not be handled as AEs/ADEs.

